### Plans for collection, laboratory evaluation, and storage of biological specimens for genetic or molecular analysis in this trial/future use {33}

Blood samples of participants will be collected on admission and 1, 3, 5, and 7 days after admission, and the samples will be transferred and handled by professional biobank technicians. Finally, serum, plasma, and white blood cell samples will be stored in West China Biobanks, certified by the China Human Genetic Resources Management Office (No. [2016]406 and No. [2022]BC0040).

## Statistical methods

### Statistical methods for primary and secondary outcomes {20a}

Data cleaning and statistical analysis will be performed by a statistician blinded to the whole trial process using the latest version of SAS software. The results of the data will be expressed as the means with ranges, medians with interquartile ranges, or numbers of patients with percentages. The comparison between the individualised CQCQD and control group is the primary interest in this study. Continuous variables are compared using the independent-sample *T* test or the Mann–Whitney *U* test (for non-normal distributions). Categorical variables are compared with the chi-squared test or Fisher’s exact test. Statistical tests will be two-sided, and *P* values < 0.05 will be considered significant.

### Interim analyses {21b}

Interim analysis is not planned in the CAP trial.

### Methods for additional analyses (e.g. subgroup analyses) {20b}

The detailed analysis strategies for subgroup analyses by the severity of AP (severe and nonsevere), age (dichotomised at 60 years old), and aetiologies of AP (hypertriglyceridaemic and non-hypertriglyceridaemic) will be compared using appropriate summary statistics (according to its distribution).

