## Introduction

### Background and rationale {6a}

Acute pancreatitis (AP) is an inflammatory disorder of the pancreas [1]. The common causes of AP such as gallstones, alcohol, hypertriglyceridaemia, endoscopic retrograde cholangiopancreatography (ERCP), and various drugs trigger self-digestion of acinar cells and induce local and systemic inflammation. It has an increasing prevalence with an overall incidence of over 34 affected cases per 100,000 person-years [2]. Most of the patients are uneventful and recover from mild disease (mild acute pancreatitis, MAP), or pull through local complications or transient organ failure defined as moderately severe acute pancreatitis (MSAP). Approximately 15–20% of patients manifesting persistent organ failure (POF) are defined as severe acute pancreatitis (SAP) [3], which are at risk of multiple organ failure (MOF) and the mortality can be up to 50% [4, 5]. Despite the global socioeconomic burden of disease, currently, there are no specific and effective therapeutic agents available to treat AP [6]. According to published guidelines [7, 8], supportive measures, such as analgesia, fluid therapy, nutritional supplementation, and organ support, remain the primary management modalities for AP patients.

Traditional Chinese medicine (TCM), which contains abundant multiple-target biologically active substances, has been broadly used in many countries and regions. Gastrointestinal dysmotility or dysfunction/failure, one of the common and complex complications in AP [9–11], is widely accepted as an important role in the pathogenesis of systemic inflammation and MOF [12–14]. Most TCM herbal formulas, such as dachengqi decoction [15, 16], qingyi decoction [17, 18], and rhubarb [19, 20], are used as an important “gut-centred” therapeutic strategy in the early treatment of AP [21]. Based on TCM theories, we summarised that the key pathogenesis of SAP-MOF is the invasion of “evil heat” to the organs, and its treatment requires “clearing heat, removing toxin, and purging the bowel” in clinical practice [22, 23]. Systematic reviews and meta-analyses of observational studies and trials with small sample sizes have demonstrated the effectiveness of rhubarb-contained TCM in reducing inflammatory markers, organ failure, local complications, and mortality, albeit the included clinical trials are of low quality [24–26].

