### Eligibility criteria {10}

The CAP trial focuses on eligible patients with predicted MSAP and SAP who are admitted within 72 h of onset. A patient will be considered eligible if he/she meets the inclusion criteria and does not meet any of the exclusion criteria.

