### Outcomes {12}

#### Primary outcome measurements

Referring to the existing study results and expert recommendations [6, 28, 29, 44], the duration of respiratory failure (SOFA score ≥ 2 points for respiratory) within 28 days after admission will be served as the primary outcome in the CAP trial.

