#### Secondary outcome measurements

I.Secondary outcomes during the index admissionThe occurrence of new-onset of any organ failure (SOFA score for respiratory, cardiovascular, or renal system ≥ 2 points) or new-onset of POF (organ failure lasts > 48 h). New onset is defined as events that occur after randomisation and not present 24 h before randomisation.Cumulative levels of C-reactive protein (CRP) on days 1, 2, 3, 5, 7, 14, 21, and 28 after admission.Levels of albumin, procalcitonin, interleukin-6 (IL-6), and neutrophil count on day 0, day 3, day 5, day 7, and day 14.Daily visual analogue scale (VAS) score of pain [45].Daily Pancreatitis Activity Scoring System (PASS) score within the 1st week after enrolment [46].Duration (days) of Systemic Inflammatory Response Syndrome (SIRS ≥ 2 points) [47].Duration (days) of fasting.The requirement of the anal tube.The requirement of prokinetic agents.Duration (days) of gastrointestinal decompression.Duration (days) of IAH and ACS.The receipt of respiratory support and renal replacement therapy.Length of intensive care unit (ICU) stays.Local pancreatic injury by contrast-enhanced computerised tomography (CECT) on days 7 and 14.Potential safety signals.Length of hospital stay.In-hospital cost.II.Secondary outcomes within 26 weeks after enrolmentThe requirement for catheter drainage or necrosectomy.Infected pancreatic necrosis.All-cause mortality.Self-report health situation by five-level EuroQol five-dimensional (EQ-5D-5L) [48].

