Outcome determination is of great importance for the trial. A recent evidence-based study suggested that trials in participants with AP should consider complications or health-related quality of life, but not mortality, as primary outcomes [6]. In the CAP trial, the duration of respiratory failure will be served as the primary endpoint. Respiratory failure constitutes a high proportion of organ failure in AP [4, 29]. In the Zangfu theory of TCM, the lung and the large intestine are interior-exteriorly related. Based on this theory, the method “purging the bowel” could potentially treat pulmonary disease [54]. The CAP trial will employ the AGI-guided algorithm for CQCQD administration to shorten the duration of respiratory failure in the early stage as a primary endpoint for SAP. Most of the secondary endpoints are registered within the index admission and follow-up patients for 6 months.

In conclusion, the CAP trial is the first pragmatic randomised controlled trial evaluating the efficacy of CQCQD in the early management of gastrointestinal and respiratory failures in predicted MSAP/SAP patients. If the CAP trial will be successfully implemented, the results would provide high-quality evidence to appraise the effects of CQCQD in AP patients.

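### The severe versus nonsevere subgroup is not fixed before randomisation; under the protocol's only definition of severe AP it is cut largely on the primary outcome

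*Protocol article*

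**What the plan says.** Four places in the protocol article bear on this point.

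- *Methods for additional analyses {20b}* plans "subgroup analyses by the severity of AP (severe and nonsevere), age (dichotomised at 60 years old" and by hypertriglyceridaemic versus other aetiology. Severity has no assessment time, no criterion and no reference to a baseline score.
- *Background and rationale {6a}* has the only definition of severe disease: "patients manifesting persistent organ failure (POF) are defined as severe acute pancreatitis (SAP".
- *Secondary outcome measurements* lists "new-onset of POF (organ failure lasts > 48 h" as an outcome, with organ failure meaning SOFA of at least 2 for the respiratory, cardiovascular or renal system. It adds: "New onset is defined as events that occur after randomisation and not present 24 h before randomisation".
- *Primary outcome measurements* takes the duration of respiratory failure, at the same respiratory SOFA threshold of 2, "within 28 days after admission will be served as the primary outcome in the CAP trial". The *Discussion* remarks: "Respiratory failure constitutes a high proportion of organ failure in AP".

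For status at entry, *Eligibility criteria {10}* says that the trial "focuses on eligible patients with predicted MSAP and SAP". The subgroup section does not use the word predicted.

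**The concern.** A subgroup comparison keeps the protection of randomisation only if treatment cannot influence who belongs to the subgroup. If severe means persistent organ failure, membership for most patients is decided after treatment has started, by the quantity the treatment is meant to change. One continuous episode of respiratory failure longer than 48 h makes a patient severe and is also a primary outcome value above 2 days.

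If the decoction works, some patients who would have had more than 48 h of failure on control have less on active treatment and are counted as nonsevere. The treated severe group has then lost its shorter episodes, and the treated nonsevere group has gained patients who would otherwise have been severe. A real benefit can look small in both subgroups, or a difference between subgroups can appear that comes from the sorting. Severity is the first subgroup named, in a trial aimed at moderately severe and severe disease, so readers are likely to use this result.

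**Working it through.** **Step 1: which definition applies.** Taken together, the passages give this chain: the subgroup is severe versus nonsevere; severe is persistent organ failure; persistent means more than 48 h at SOFA of at least 2; the primary outcome is the time spent at respiratory SOFA of at least 2. No baseline rule in the article is labelled severe. HAPS only excludes predicted mild disease, and BISAP/GCS at allocation guides monitoring and dosing.

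**Step 2: what this does to the comparison.** There is no subgroup figure in the protocol to reproduce. Its *Sample size {14}* section gives a 2-day effect and an SD of 4.5 days, but no control mean, no share of patients with respiratory failure and no distribution. Those three are assumptions here:

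- A share of 0.6 has respiratory failure; the rest have duration 0.
- Durations among those with failure follow a gamma distribution with shape 1.5 and mean 6 days (scale 6/1.5 = 4), capped at 28 days.
- Severe is taken as duration above 2 days.

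Plausibility check (ignoring the cap): overall control mean 0.6 × 6 = 3.6 days; variance 0.6 × (1.5 × 4² + 6²) - 3.6² = 36 - 12.96 = 23.04; SD 4.8 days, near the protocol's 4.5.

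Two ways in which treatment could work, with G the gamma duration:

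- *Shift*: 2 days off every episode, not below 0. A treated patient is labelled severe only if the untreated duration exceeds 4 days.
- *Proportional*: every episode shortened by 30%. A treated patient is labelled severe only if the untreated duration exceeds 2/0.7 = 2.86 days.

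Shares labelled severe:

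- Control: 0.6 × P(G > 2) = 0.48
- Shift: 0.6 × P(G > 4) = 0.34
- Proportional: 0.6 × P(G > 2.86) = 0.42

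Mean duration among those labelled severe, by simulation, is 7.2 days on control, 6.9 under the shift and 5.5 under the proportional effect. The true effect in a fixed stratum (patients whose untreated duration exceeds 2 days) is -2.0 under the shift, and -0.30 × 7.2 = -2.2 under the proportional effect.

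| Effect | Overall | Seen in severe | True, fixed stratum | Severe, control / treated |
|---|---|---|---|---|
| 2-day shift | -1.1 | -0.3 | -2.0 | 48% / 34% |
| 30% proportional | -1.1 | -1.7 | -2.2 | 48% / 42% |
| None | 0 | 0 | 0 | 48% / 48% |

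**Step 3: sensitivity to the assumed durations.** With everyone given a gamma duration, SD about 4.5 days and control mean 3 to 8 days, the 2-day shift shows between +0.36 (mean 3) and -1.07 (mean 8) in the severe subgroup, against a true -2.0. A proportional effect that lowers the mean by 2 days shows -2.91 against -4.44 (mean 3) and -1.89 against -2.06 (mean 8). When 40% have no failure and the control mean is 5 days, almost nobody crosses 48 h and the bias nearly vanishes: -1.92 against -2.00 for the shift, -3.31 against -3.33 for the proportional effect.

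**The case against.** The strongest reply is that the reading through persistent organ failure is inferred. The subgroup section does not mention it, and the definition comes from a background paragraph. A reader might go further and conclude that an admission measure is ruled out, since everyone enrolled is already predicted moderately severe or severe. That does not follow. The predicted population pools two grades, and the protocol already splits enrolled patients at allocation by BISAP/GCS of at least 2 versus below 2. Some patients may also have organ failure before randomisation: entry is allowed up to 72 h from onset, and only a SOFA score above 3 for an individual organ is excluded. A baseline meaning was therefore possible. What remains is that no text assigns it, while the one definition given points to a later status.

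A reader might also object that the section plans no treatment-by-subgroup interaction test. The article neither prescribes nor excludes one, and an analysis plan not shown may contain it, so this is not part of the point.

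The reply is also right on size. Prevalence, mean and distribution are assumed; the 2-day shift is an unfavourable mechanism; and under a proportional effect about three quarters of the true effect stays visible (1.7/2.2 = 0.77). The calculation treats severe as respiratory duration alone, whereas cardiovascular and renal failure also count, so the overlap with the primary outcome is large but incomplete.

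Finally, the trial calls its framework exploratory, and this is one of three additional subgroup factors.

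**Conclusion.** The point stands in a conditional form. The protocol does not fix severity before randomisation, and the only definition it offers makes the subgroup depend on a status that is, for most patients, settled afterwards and largely shared with the primary outcome. Under that definition, and if the decoction shortens organ failure as the trial hypothesises, the within-subgroup comparisons are biased.

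The documents do not determine how much. In the worked example the severe subgroup shows between about one sixth (0.3/2.0) and about three quarters (1.7/2.2) of the true effect, depending on how treatment acts. Other assumed durations gave anything from a reversed sign to almost no bias. A reader might infer that the subgroup result is certain to be wrong or that the trial's randomised comparison is lost. Neither is supported: with no treatment effect there is no bias, and the primary comparison, the sample size and the age and aetiology subgroups are not touched. It should be fixed before analysis, as a matter of moderate weight.

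**What to change.** In *Methods for additional analyses {20b}*, define the severity subgroup by a variable recorded before randomisation. Two candidates are already assessed: BISAP/GCS of at least 2 versus below 2 at allocation, or respiratory SOFA of at least 2 versus below 2 at admission. If the first is chosen, state which score or combination counts, because the protocol writes the two as alternatives. Report final severity, defined by persistent organ failure, only as an outcome by arm and not as a grouping variable. If the sponsor always meant a baseline measure, the same sentence settles it.

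The cost is one sentence in the protocol or analysis plan, agreed before unblinding. It needs no new data and no change in sample size.

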#### Inclusion criteria

Patients will be included if they fulfil all the following criteria:Meet the diagnostic criteria of AP [3], which fulfil two of the following three items: typical symptoms and signs of abdominal pain, elevated serum amylase and/or lipase at least three times the upper limit of normal, and AP characteristic image findings.Aged between 18 and 75 years, male or female.Admitted to Pancreatitis Centre Ward within 72 h of disease onset.Written informed consent obtained.

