### Sample size {14}

The sample size calculation was based on the following assumptions: a reduction in duration of respiratory failure of 2 days in the treatment group, and a standard deviation of 4.5 days for each group [17, 29]. Assuming that the significance level is 0.05 and the study power is 0.8 (two-sided *α* = 0.05, *β* = 0.2), we projected a sample size of 111 patients in each group using Power Analysis & Sample Size software (PASS statistic software, version 11.0.7, NCSS). Considering a 10% dropout rate, a total of 248 patients will be recruited in this trial with 124 patients for each group.

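### A single split at 60 years is an inefficient way to ask whether the treatment effect changes with age in an 18-75 population

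*Protocol article*

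**What the plan says.** Section {20b} of the protocol article names three subgroup factors: severity, aetiology and age. For age it fixes the form of the variable as "age (dichotomised at 60 years old", and it says that the subgroups "will be compared using appropriate summary statistics (according to its distribution". It gives no reason for the cut at 60, no expected number of patients on either side and no analysis of age in years.

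The inclusion criteria admit patients "Aged between 18 and 75 years, male or female", so age is known for everyone. The section on statistical methods {20a} names a t test or a Mann-Whitney U test for continuous outcomes and no regression model. The trial design section {8} describes the framework as exploratory.

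**The concern.** A split at 60 treats patients of 20 and 59 as alike and patients of 59 and 61 as different. It also lies 42 years above the lower age limit and 15 below the upper one, so it may divide the sample unequally. Both features weaken any statement on whether the effect depends on age, although the data for a fuller analysis are already held. The risk is that a wide and possibly chance result in the older group is read as evidence for or against an age effect.

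This is separate from the choice of test. Even a proper interaction test on the split would not use the information within each age group.

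**Working it through.** **Inputs from the protocol.** Cut at 60 {20b}; ages 18-75 (inclusion criteria). From the sample size section {14}: "a reduction in duration of respiratory failure of 2 days in the treatment group", "a standard deviation of 4.5 days for each group", 111 per group (222 evaluable) and 248 recruited.

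**The plan's own figure.** No figure is given for the age subgroup. For the whole trial, the stated inputs give n = 2 × (1.96 + 0.84)² × 4.5² / 2² ≈ 80 per group (81 with the t distribution), not 111. At 111 per group the power is 0.91. The dropout step does reproduce: 111 / 0.9 = 123.3, rounded up to 124, hence 248. The gap between 80 and 111 is a separate matter, and the information fractions below do not depend on the sample size.

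**Information kept by the cut.** For a linear change of effect with age, the fraction kept is the squared correlation between age and the indicator of being 60 or over. For uniform ages it is 3p(1 − p), with p = 15/57 = 0.263, giving 3 × 0.263 × 0.737 = 0.58. For normal ages truncated to 18-75 it was simulated. The means and SDs are assumptions and refer to the distribution before truncation.

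| Assumed ages | Share 60 or over | Older patients of 248 | Kept | Lost |
|---|---|---|---|---|
| Uniform 18-75 | 26% | 65 | 58% | 42% |
| Mean 42, SD 12-14 | 7-10% | 16-24 | 28-35% | 65-72% |
| Mean 45, SD 12-14 | 10-13% | 25-33 | 35-40% | 60-65% |
| Mean 50, SD 12-14 | 19-21% | 47-52 | 46-49% | 51-54% |
| Mean 55, SD 12-14 | 31% | 76-77 | 57% | 43% |
| Mean 60, SD 12-14 | 42-44% | 104-109 | 62-64% | 36-38% |

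A younger or tighter distribution loses more (mean 42, SD 10: 82%).

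**Precision in the older group.** With 222 evaluable patients and n older patients per arm, the 95% half-width is 1.96 × 4.5 × √(2/n). Power for a 2-day effect is Φ(2/SE − 1.96), with SE = 4.5 × √(2/n).

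| Share 60 or over | n per arm | Half-width (days) | Power for 2 days |
|---|---|---|---|
| 10% | 11.1 | 3.7 | 0.18 |
| 20% | 22.2 | 2.6 | 0.32 |
| 26% | 28.9 | 2.3 | 0.39 |
| 40% | 44.4 | 1.9 | 0.55 |

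Power to detect a 2-day difference between the effects in the two age groups is 0.17, 0.26, 0.31 and 0.37 for these shares.

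**What age in years would gain.** Take an assumed change of 1 day per 10 years of age and 248 patients. The SE of the interaction slope is √(4 × 4.5² / (248 × variance of age)). At mean 50 and SD 14 the SD after truncation is 12.3, so SE = √(81 / (248 × 151.3)) = 0.0465 and 0.10 / 0.0465 = 2.15. Power is Φ(2.15 − 1.96) ≈ 0.58. With the cut the ratio falls to 2.15 × √0.49 = 1.51, and power to about 0.33. Over means 42-56 and SDs 12-14, power is 46-58% with linear age and 18-35% with the cut. At half that slope it is 15-19% against 8-12%.

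**The case against.** The strongest reply is that this is a preference. One conventional age split is pre-specified, nothing is contradicted, and the section promises only summary statistics. A fuller age model could sit in an analysis plan that is not shown. That limits the weight of the point but does not remove it, because the protocol itself settles the form of the age variable as a split.

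A second reply is that the remedy does not make the question answerable. This largely stands. A slope of 1 day per 10 years means a shift of 5.7 days across 18-75, nearly three times the 2-day design effect, and power with linear age is still only about half. Modelling adds no older patients; intervals at older ages narrow through the assumed age shape. The protocol also names no regression to which a term could simply be added.

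Three stronger readings are tempting and not supported:

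- A reader might infer that the split always wastes half or more of the information. With uniform ages or a mean of 55 the loss is 42-43%, and with a mean of 60 it is 36-38%.
- A reader might infer that the older group must be small. At a mean of 60 it exceeds 40% of patients.
- A reader might infer that the older group's interval is bound to be uninformative against the 2-day effect. The half-width drops to 1.9 days at a 40% share. The full width does not discriminate, because even the whole trial at 124 per arm has a half-width of 1.12 days and a full width of 2.24.

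**Conclusion.** The concern holds in a limited form. Under a smooth change of effect with age, the cut loses about 35-70% of the interaction information over assumed mean ages of 42-60 with SD 12-14, and for uniform ages. The size rests on an age distribution that the document does not give, and on linearity. A true step at 60 would lose nothing, but the protocol claims no such threshold. For most of these mixes the older group is a minority with an imprecise estimate.

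The consequence is confined to one subgroup analysis in a trial described as exploratory. The primary comparison, the sample size and the conduct of the trial are not affected. It is a worthwhile refinement and not a fault that threatens the trial.

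**What to change.** In section {20b}, make the age analysis a treatment-by-age interaction with age in years. Section {20a} names only two-group tests, so state that a regression of the primary outcome on treatment, age and their product is added for this purpose, with standard errors robust to non-normal durations. Report the estimated treatment effect with its 95% interval across the age range, check linearity with a simple curve, and keep the 60-year split as a descriptive display.

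The cost is a change of wording and one extra exploratory model, with no new data. The downside is an assumed age shape, which the curve helps to check. Because power stays modest, the text should say that the result is exploratory and that failure to find an interaction does not show that the effect is constant with age.
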